#### Cognitive tasks

The cognitive tasks will be common to both parts of the study.

The tDCS effects on delay discounting will be assessed using the Monetary Choice Questionnaire (MCQ) [29]. The MCQ is a task composed of 27 items of hypothetical monetary choices between smaller immediate rewards and larger delayed ones. The rewards can be small, medium, or large and vary from 11 to 85€. The delays vary between 7 and 186 days. The calculation of delay discounting is based on the hyperbolic function V = A/ (1 + *k*D). V represents the subjective value of the delayed reward, A is the amount of the delayed reward, D is the delay, and *k* is the coefficient that estimates the subjective discounting rate for the given delayed reward. *K*-values will be generated by the 27-item MCQ Automated Scores [30] for overall discounting rates of each subject and will be compared before and after the tDCS session (jumpers) or before and after the first and the last tDCS session and at day 12 and day 30 of each sequence (cyclists).

The tDCS effects on different aspects of impulsivity will be assessed using four tasks: the French version of the Barratt Impulsiveness Scale (BIS-10), the experimental Go/No-Go and Stroop tasks, and the Balloon Analog Risk Task (BART).

The BIS-10 is a 34-item self-report questionnaire that measures overall and specific impulsivity (cognitive, motor, and non-planning impulsivity) [31]. Each item is rated 0, 1, 3, or 4 points and the overall scores of impulsivity thus vary from 0 to 136.

The Go/No-Go task is issued from the Frontal Assessment Battery [32]. The subjects must inhibit a response that was previously given to the same stimulus (e.g., not tapping when the examiner taps twice), in order to assess their difficulties in controlling impulsivity. The scores range from 0 to 3 depending on the number of errors.

The Stroop task is issued from the GREFEX battery [33]. This task is divided into three parts: a naming task (where the subject quotes colours as quickly as possible), a reading task (where the subject reads the name of the colours as quickly as possible), and an interference task (where the subject names the colour they observe and not the one that is written as quickly as possible). The interference is obtained by subtracting the denomination time from the interference time.

The BART task is a computer-based measure of the risk-taking [34]. During this task, the subjects must press a button to inflate a series of 30 balloons displayed on the computer. Each pump corresponds to 5 cents, which are accumulated in a temporary bank (the amount of which is unknown to the subject). At any time, the subjects can collect the money obtained in a definitive bank (the amount of which is displayed on the computer). However, if the balloon explodes before collection, the money accumulated in the temporary bank is lost and a new balloon appears on the screen. Each balloon has a different probability of explosion and the subject’s objective is to make as much money as possible. Risk-taking behaviour will be measured by the adjusted average number of pumps (only trials in which the balloons did not explode are included in the calculations).

The tDCS effects on motivation will be measured using the Effort Expenditure for Rewards Task (EEfRT) [35]. It is a computerised effort-based decision-making task. For each trial, the subject must choose between an easy and a difficult task.

During the easy task, the subject must press the “L” key on the keyboard with the index finger of the right hand and can earn 1€ according to the probability of retribution. During the hard task, the subject must press the “S” key with the pinkie of the left hand and can earn between 1.24 and 4.30€ (“reward magnitude”) according to the probability of retribution. The probability of reward retribution varies at each trial; an indication of this probability (12%, 50%, or 88%) is given before the choice. The subject thus makes a choice between easy and difficult tasks according to the probability of reward and the reward magnitude. Motivation is modelled by the percentage of hard task choices.

All of these tasks will be performed before and after each tDCS session (jumpers), or before and after the first and the last tDCS session, and at day 12 and day 30 of each sequence (cyclists).

A comparison of inter-condition scores and scores before and after tDCS session/sequence will be made.

Finally, depression severity will be assessed by the clinician (QIDS-C16) and self-reported by the subject (QIDS-SR16) [36].

The QIDS-SR16 has 16 items (score range from 0 to 27) assessing the severity of depressive symptoms as perceived by the subject, with the following cut-off points: 0–5 none; 6–10 mild; 11–15 moderate; 15–20 severe; and 21–27 very severe depression.

The QIDS-C16 has 16 items (score range from 0 to 27) assessing the severity of depressive symptoms as perceived by the psychiatrist, with the same cut-off points.

These depression scales will be applied at participant’s inclusion and after the last session or sequence of tDCS.

#### Pointing task

In part A, evaluation of the acute effect of tDCS on fine motor performance will also be performed, by means of a visual pointing task. In a sitting position, participants will have to point with a pencil (dominant hand) between two targets as accurately and as fast as possible. The targets are black squares designed on paper displayed on the table in front of the participant. The distance between participants’ trunk and the table and targets will be kept constant between each measurement. The targets will be displayed in a frontal axis, with the nearest target aligned with the shoulder and the furthest target shifted by 45° on the left. Three different levels of target difficulty will be set according to target widths and distances between them. Three widths (W = 0.5, 1.5, and 4 cm) and three centre-to-centre target distances (D = 15, 20, and 35 cm) will be used to manipulate the index of difficulty (ID), calculated by the formula: ID = log2(2D/W). One trial will consist of five cyclical pointing movements as accurately and as fast as possible between two targets of the same size, namely ten arm movements, always starting and finishing on the nearest target. The total time to perform these ten movements is taken into account for each trial. Two trials will be performed per ID (total of six trials). Subjects will have to perform the pointing task under real conditions but also to imagine themselves performing these six trials. They will be particularly instructed to feel pointing between the targets (kinesthetic imagery) as they would actually do [37]. They will be asked not to track the targets visually. The comparison of imagined and real trials therefore provides different clues about the different stages of the movement, from movement planning to programming, and execution of the considered task [38].

### Outcomes

Our efficacy criteria will be the evaluation of neuromuscular performance during an explosive task (main outcome, part A) or during an endurance task (secondary outcomes, part B).

In part A, we will compare the height of the vertical jumps (in centimetres) or the length of horizontal jumps (in centimetres) performed before and after active or sham tDCS session. In part B, endurance performance will be assessed by comparing the average power output (in watts) during a time-trial realised before, after the first, on the last tDCS session, and at day 12 and day 30 of each sequence.

Secondary efficacy criteria include:
tDCS effects on the neuromuscular system by analysis of the EMG signals during MVC, evoked potentials (muscle and spinal excitability, voluntary activation), and comparison of the results obtained before and after tDCS session (jumpers) or before and after the first and the last tDCS session, and at day 12 and day 30 of each sequence (cyclists)tDCS effects according to the motor expertise by comparison of performance (in centimetres for vertical jump heights and horizontal jump lengths) between amateur subjects and those with high-level jump practice, or sedentary and amateur subjects and those with high-level cycling practicetDCS effects on motor gestures and speed–accuracy trade-offs during a pointing task before and after the tDCS session (jumpers), by analysing times (in seconds) to complete the different pointing tasksChanges in the rating of perceived exertion and muscle pain by comparison of the scores from the Borg CR10 scale (from 1 to 10) and the Cook’s scale (from 1 to 10) obtained during the endurance task (every two minutes) before and after the first and the last tDCS session and at day 12 and day 30 of each sequence (cyclists)Changes in motivation, by comparison of scores from the EEfRT (from 0 to 100) obtained before and after the tDCS session (jumpers) or before and after the first and the last tDCS session and at day 12 and day 30 of each sequence (cyclists).tDCS effects on impulsivity by comparison of the scores from BIS-10 (from 0 to 136), the experimental Go/No-Go (from 0 to 3), Stroop (interference score) tasks, and the BART (adjusted average number of pumps) obtained before and after the tDCS session (jumpers) or before and after the first and the last tDCS session, and at day 12 and day 30 of each sequence (cyclists)Changes in delay discounting, by comparison of the scores from the MCQ (from 0.00016 to 0.24,942) obtained before and after the tDCS session (jumpers) or before and after the first and the last tDCS session and at day 12 and day 30 of each sequence (cyclists)Changes in depression severity, by comparison of scores from the QIDS-SR16 and QIDS-C16 (from 0 to 27) obtained at the inclusion and after the last tDCS session (jumpers) or the last tDCS sequence (cyclists)

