### Sample size

Our sample size calculation is based on the primary efficacy outcome that relates to changes in motor performance before and after a tDCS session during an explosive task (jumps). In a previous study, Lattari et al. [22] showed an 11.2% improvement in the height of the CMJ following a tDCS session, corresponding to a difference of 3.9 cm (Table 1 of Lattari’s et al.). We expect a 15% improvement in our study corresponding to a difference of 5.1 cm. No difference is expected in the sham tDCS group. Considering a significance level of 5%, a power of 90%, and a standard deviation for paired differences of 6.5 (calculated from standard deviations, page 21, Table 1 with an hypothesis of a covariance of measures of 50%), 20 jumpers are included to meet the objectives of the study. Sample size calculation was performed on PASS 13 Power Analysis and Sample Size Software (2014) [39, 40] .

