### Data management and statistical analyses

All collected information will be registered in physical files (case report files (CRFs)), previously anonymised with the participant’s randomisation code in order to respect confidentiality at all times. Computer test data (BART, EEfRT) and physical test results will be collected in electronic format.

All researchers and trained staff called upon to collaborate in the tests are bound to secrecy.

Analyses will be performed using the SAS® 9.4 Software for Windows (SAS Institute©, Cary, NC, USA). Categorical variables will be described in terms of effective, absolute, and relative frequencies for each modality. Continuous variables will be described in terms of minimum and maximum, quartiles, means, and standard variations. Two-way repeated measures ANOVAs will be performed with the within-group factors of condition (a-tDCS/ c-tDCS/sham-tDCS) and moment (pre- and post-tDCS) for endurance performance or explosive performance. Bonferroni corrections will be employed to correct for type I errors due to multiple testing. The sphericity assumption will be tested using the Mauchly’s test and the Greenhouse-Geisser correction will be used whenever data sphericity is violated. The level of significance will be set at *p* ≤ 0.05. Subgroup analysis (level of practice) will be descriptive because of the small sample size of the study. Means and proportions will be calculated with their 95% confidence interval. All valid data will be used at different times of the study. There is no strategy for replacing missing data.

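### The part A main outcome covers three jumps with none named primary, while the sample size rests on the countermovement jump alone at an uncorrected 5% and the Bonferroni family is undefined

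*Protocol article*

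**What the plan says.** Outcomes makes performance in the explosive task the main outcome of part A and defines it this way: "we will compare the height of the vertical jumps (in centimetres) or the length of horizontal jumps (in centimetres"), before and after active or sham stimulation. The sections Study setting and overview and Explosive or endurance task show that this means three tests: squat jump (SJ), countermovement jump (CMJ) and standing long jump (SLJ). None is singled out.

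Sample size takes its effect from an earlier study that "showed an 11.2% improvement in the height of the CMJ following a tDCS session", a difference of 3.9 cm. It continues: "We expect a 15% improvement in our study corresponding to a difference of 5.1 cm". The error rates and spread follow: "Considering a significance level of 5%, a power of 90%, and a standard deviation for paired differences of 6.5". The result is that "20 jumpers are included to meet the objectives of the study". No adjustment of the 5% is mentioned.

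Data management and statistical analyses plans a repeated-measures ANOVA with condition and moment as factors, and then states: "Bonferroni corrections will be employed to correct for type I errors due to multiple testing". It does not say which tests form the family.

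The Background states the main objective as the comparison of left dlPFC stimulation with sham. Part A also has a second active condition, over the right motor cortex.

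**The concern.** The outcome, the error rate used for sizing and the correction rule are all stated in this article, but they describe different numbers of tests. The sizing describes one test. The outcome describes three, joined by a word that leaves open which of them decides the trial. The correction rule could cover the three jumps or not.

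Two things are at stake. If the correction covers the jumps, the power for the sized outcome is lower than stated. If it does not, any one of three jumps can be reported as the primary result, each at 5%, and the overall false-positive rate exceeds the stated level. The choice between these could be made after the data are seen.

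**Working it through.** **Inputs from Sample size:** difference 5.1 cm, SD of paired differences 6.5 cm, significance level 5%, power 90%, n = 20. **Input from Study setting and overview:** three jumps. **Assumptions:** tests are two-sided (the section does not say); the correlation between the jumps' changes is not given and is varied from 0.5 to 0.9.

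**1. Reproducing the protocol's figure.** Paired t-test, power from the noncentral t distribution.
- Standardised effect = 5.1 / 6.5 = 0.785.
- Noncentrality = 0.785 × √20 = 3.51.
- Critical value, 19 degrees of freedom, two-sided 5%: 2.093.
- Power = 91.4%. At n = 19 it is 89.8%, so 20 is the smallest number reaching 90%.

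The stated 20 is reproduced exactly with a two-sided, uncorrected 5%. A one-sided test would have given 16.

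**2. If Bonferroni covers the three jumps.**
- Per-test level = 0.05 / 3 = 0.0167; critical value, 19 degrees of freedom: 2.625.
- Noncentrality unchanged at 3.51.
- Power for CMJ at n = 20: 80.1%.
- Power at n = 24 is 88.6% and at n = 25 is 90.1%, so 25 jumpers are needed for 90%.

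**3. If Bonferroni covers only comparisons within each ANOVA, so each jump is tested at 5%.** With independent jumps the chance of at least one false positive would be 1 − 0.95³ = 14.3%. The jumps are made by the same people and are surely correlated. Simulated paired t-tests with n = 20 and no true effect give:

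| Correlation between jumps | At least one false positive |
|---|---|
| 0.5 | 13% |
| 0.7 | 11% |
| 0.9 | 9% |

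**4. A different success rule.** Suppose a win on any jump counts, Bonferroni covers the three, and every jump has the CMJ standardised effect of 0.785. The chance of at least one significant jump is then between about 88% (correlation 0.9) and 96% (correlation 0.5). The 80% in step 2 is therefore power for one given jump, not for any jump.

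**The case against.** The best defence is that the Bonferroni sentence stands between the ANOVA and the sphericity test, and so may refer only to post hoc comparisons within each ANOVA, or to the long list of secondary outcomes. Its family could be defined in an analysis plan that is not shown. Sizing CMJ at 5% is compatible with that. This stands: a reader might infer that the sample size and the correction rule flatly contradict each other, but the documents show an ambiguity. It does not rescue the outcome definition, because on that reading the three jumps are uncorrected and step 3 applies.

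A reader might also count six primary tests, three jumps by two active-versus-sham contrasts. The Background limits the main objective to left dlPFC versus sham, and nowhere is the motor cortex contrast called primary. Three tests is the supported family.

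Nor does Bonferroni take away the trial's power. It lowers CMJ power from 91% to 80%, and under an any-jump rule power may stay near or above 90%, as step 4 shows. That result, however, needs SJ and SLJ to share the CMJ effect, and the protocol gives no effect or SD for either.

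Finally, the title calls the trial exploratory. That tempers the severity, but the Background calls it a superiority trial and Sample size claims 90% power for a primary outcome, so those figures should match what will be tested.

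**Conclusion.** The point holds in this form: no jump is named primary, the sizing uses CMJ alone at an uncorrected 5%, and the scope of Bonferroni is open. On the protocol's inputs, CMJ power is 91% if it is the only primary test and 80% if the correction spans the three jumps. Without correction across the jumps, the false-positive rate is about 9% to 13%. On this calculation the stated 5% and 90% hold together only with a single primary jump.

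The power figures assume two-sided tests and the protocol's own 5.1 cm and 6.5 cm. The false-positive range depends on the assumed correlations. Whether 6.5 cm is also the right SD for the difference between active and sham changes is a separate question, and nothing here relies on it. Because the choices needed are already implied in the text and the trial is labelled exploratory, this should be fixed but does not call the design into question.

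**What to change.** - **Outcomes:** name one primary test for part A: CMJ height, left dlPFC versus sham, at two-sided 5%. CMJ is the outcome that was sized, and this is the contrast in the main objective. List SJ, SLJ and the M1 contrasts as secondary.
- **Data management and statistical analyses:** state that Bonferroni applies to the secondary comparisons, and which they are.

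The cost is a sentence in each section and the loss of primary status for SJ and SLJ. The multiplicity problem then needs no extra participants.

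If the investigators prefer to keep all three jumps primary, they should define the Bonferroni family as those three. They should then either restate power as about 80% per jump with 20 jumpers, or recruit 25 for 90%. Both figures assume the same standardised effect for each jump, which should be said.

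### The pointing task's speed-accuracy outcome is scored on time only, so a shift toward speed at the cost of accuracy cannot be told from a real gain

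*Protocol article*

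**What the plan says.** The Pointing task section of the protocol article presents the task as the test of acute tDCS effects on fine motor performance in part A. Under its instruction, "participants will have to point with a pencil (dominant hand) between two targets as accurately and as fast as possible". The accuracy demand is built into the design: "Three different levels of target difficulty will be set according to target widths and distances between them". The section lists widths of 0.5, 1.5 and 4 cm and centre-to-centre distances of 15, 20 and 35 cm, defines ID = log2(2D/W), and plans two trials per ID, six in all. Each trial has ten arm movements. The same six trials are also imagined.

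The quantity kept is stated at trial level: "The total time to perform these ten movements is taken into account for each trial". The Outcomes section repeats it at outcome level, where the criterion covers "speed–accuracy trade-offs during a pointing task before and after the tDCS session (jumpers), by analysing times (in seconds) to complete" the various tasks. Neither section names a count of misses, an endpoint error, or a rule for a trial in which a target was missed.

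**The concern.** Participants are asked for two things, accuracy and speed, and one of them is scored. The nominal ID describes the task actually performed only if the pencil lands inside the target. A participant who speeds up by letting the pencil land more widely performs an easier task than the nominal one, yet enters the analysis simply with a shorter time.

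The sham control and the blinding do not remove this, because the change in strategy could itself be caused by stimulation. The Background justifies the left dlPFC target partly by its role in cognitive control and decision-making. The Discussion allows for either improvement or disruption of impulsivity. A shorter time after active than after sham stimulation could therefore be reported as better fine motor performance when some or all of it is less care.

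**Working it through.** **1. The plan's own count.** 3 difficulty levels × 2 trials = 6 trials, which agrees with the stated six.

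**2. Difficulty levels available.** ID = log2(2D/W), in bits, from the stated widths and distances:

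| D (cm) | W = 0.5 | W = 1.5 | W = 4 |
|---|---|---|---|
| 15 | 5.91 | 4.32 | 2.91 |
| 20 | 6.32 | 4.74 | 3.32 |
| 35 | 7.13 | 5.54 | 4.13 |

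Three of these nine pairs are used. The article does not say which. Possible IDs run from 2.91 to 7.13 bits, so a relation of time to ID can be estimated.

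**3. Can time by ID detect a loss of accuracy?** Assume a linear relation, T = a + b·ID. Let endpoint spread grow by a factor r at every level. The difficulty actually performed becomes ID − log2(r), so

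T = a + b·(ID − log2 r) = (a − b·log2 r) + b·ID.

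The slope is unchanged and only the intercept falls. A true gain of c seconds at every level gives T = (a − c) + b·ID. The two are identical when c = b·log2(r). If the spread grows by a different factor at each level, the three times can take any pattern. Times alone therefore cannot separate the two explanations.

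**4. Illustration by spread.** Assumptions that are not in the document: pairings 35/0.5, 20/1.5 and 15/4 cm, spread initially matching the nominal width, and r = 1.5. The loss is log2(1.5) = 0.585 bits at each level:

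- 7.13 to 6.54 bits (0.585/7.13 = 8%)
- 4.74 to 4.15 bits (0.585/4.74 = 12%)
- 2.91 to 2.32 bits (0.585/2.91 = 20%)

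If time is also assumed proportional to ID (a = 0), time falls by the same percentages with no change in motor ability.

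**5. Illustration by miss rate.** Assumptions that are not in the document: normal endpoints centred on the target, and an effective width of 4.133 SD, which makes about 4% misses equivalent to the nominal width. For miss rate m, SD = (W/2)/z(1 − m/2), and the loss is log2(4.133·SD/W).

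| Misses | Effective/nominal width | Bits lost | Share of 7.13 | Share of 4.74 | Share of 2.91 |
|---|---|---|---|---|---|
| 4% | 1.01 | 0.01 | – | – | – |
| 10% | 1.26 | 0.33 | 4.6% | 6.9% | 11.3% |
| 20% | 1.61 | 0.69 | 9.7% | 14.5% | 23.7% |
| 30% | 1.99 | 1.00 | 14.0% | 21.0% | 34.2% |

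The two routes give effects of the same order. Neither says what will happen in this trial.

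**The case against.** The strongest reply is that accuracy is controlled by design rather than measured afterwards. Width and distance are varied, the instruction asks for accuracy, and time across three IDs is a workable description of a speed-accuracy trade-off. That stands as far as it goes. A reader might infer that the named outcome cannot be derived at all, and the document does not support that. What remains is the condition that the targets are hit, which the instruction implies but no stated measure checks.

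Second, a journal article condenses. A rule for failed trials may sit in the full protocol or the case report form. This also stands in part: a reader might infer that misses go unrecorded or that trials with misses are kept unrepeated, and the article says neither. The point rests instead on the measure that is stated, in two places, as time. Where errors do enter a score, as in the Go/No-Go task, the article says so.

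Third, imagined trials yield only a time, so time is the one measure common to real and imagined trials. That is a good reason to keep time, but not a reason to leave accuracy out of the real trials.

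Fourth, the Background cites a benefit of tDCS on cognitive function, which would suggest more control rather than less care. Go/No-Go, Stroop, BART and BIS-10 are also given before and after each jumper session and could show a general shift to hastier responding. Both remarks are fair, and the direction of any bias is not established. But those tests do not record where the pencil landed and cannot correct the pointing times.

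**Conclusion.** The point holds as a minor one. With completion time as the only stated measure, a faster but less accurate real trial counts as a gain, and analysing by nominal ID does not reveal it. The algebra rests on a linear time-ID relation, and the exact equivalence with a uniform speed gain on a common rise in spread.

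The size is unknown. A reader might take the 8% to 20%, or the 4.6% to 34.2% from the miss-rate route, as an expected bias. They are not: the pairings, spread, miss rates, baseline and zero intercept are all assumed.

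The scope is one secondary outcome of part A in a trial titled exploratory. The jump outcomes and the sample size of 20, which is built on CMJ height, are untouched.

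**What to change.** For the real trials:

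- Use a fresh target sheet for each trial and count the contacts outside the target, out of ten.
- Analyse time by ID together with the miss count.
- Claim improved pointing only if time falls without more misses. Show the active-minus-sham difference in misses with its 95% confidence interval, because there are only 20 contacts per participant, level and time point (2 trials × 10).
- State how a trial with misses is handled.

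Keep time alone for the imagined trials and for the real-versus-imagined comparison. Leave out an analysis by effective ID unless marks inside the targets can be read; the targets are black squares, so endpoint spread may not be legible, although marks outside them should be. For jumpers already tested whose sheets were not kept, report the result as completion time and say that accuracy was not assessed.

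The cost is one printed sheet per real trial: 6 trials × 2 time points = 12 per visit, × 3 visits = 36 per jumper, × 20 jumpers = 720 in all. There is also a little more counting and data entry. No new equipment is needed.
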